# SCARLET (Supplemental Citicoline Administration to Reduce Lung injury Efficacy Trial): study protocol for a single-site, double-blinded, placebo-controlled, and randomized Phase 1/2 trial of i.v. citicoline (CDP-choline) in hospitalized SARS CoV-2-infected patients with hypoxemic acute respiratory failure

**DOI:** 10.1186/s13063-024-08155-0

**Published:** 2024-05-18

**Keywords:** Lung, SARS CoV-2, COVID-19, Influenza, Acute respiratory failure, Hypoxemia, CDP-choline, Citicoline

## Abstract

**Background:**

The SARS CoV-2 pandemic has resulted in more than 1.1 million deaths in the USA alone. Therapeutic options for critically ill patients with COVID-19 are limited. Prior studies showed that post-infection treatment of influenza A virus-infected mice with the liponucleotide CDP-choline, which is an essential precursor for de novo phosphatidylcholine synthesis, improved gas exchange and reduced pulmonary inflammation without altering viral replication. In unpublished studies, we found that treatment of SARS CoV-2-infected K18-hACE2-transgenic mice with CDP-choline prevented development of hypoxemia. We hypothesize that administration of citicoline (the pharmaceutical form of CDP-choline) will be safe in hospitalized SARS CoV-2-infected patients with hypoxemic acute respiratory failure (HARF) and that we will obtain preliminary evidence of clinical benefit to support a larger Phase 3 trial using one or more citicoline doses.

**Methods:**

We will conduct a single-site, double-blinded, placebo-controlled, and randomized Phase 1/2 dose-ranging and safety study of Somazina® citicoline solution for injection in consented adults of any sex, gender, age, or ethnicity hospitalized for SARS CoV-2-associated HARF. The trial is named “SCARLET” (Supplemental Citicoline Administration to Reduce Lung injury Efficacy Trial). We hypothesize that SCARLET will show that i.v. citicoline is safe at one or more of three doses (0.5, 2.5, or 5 mg/kg, every 12 h for 5 days) in hospitalized SARS CoV-2-infected patients with HARF (20 per dose) and provide preliminary evidence that i.v. citicoline improves pulmonary outcomes in this population. The primary efficacy outcome will be the S_p_O_2_:F_i_O_2_ ratio on study day 3. Exploratory outcomes include Sequential Organ Failure Assessment (SOFA) scores, dead space ventilation index, and lung compliance. Citicoline effects on a panel of COVID-relevant lung and blood biomarkers will also be determined.

**Discussion:**

Citicoline has many characteristics that would be advantageous to any candidate COVID-19 therapeutic, including safety, low-cost, favorable chemical characteristics, and potentially pathogen-agnostic efficacy. Successful demonstration that citicoline is beneficial in severely ill patients with SARS CoV-2-induced HARF could transform management of severely ill COVID patients.

**Trial registration:**

The trial was registered at www.clinicaltrials.gov on 5/31/2023 (NCT05881135).

**Trial status:**

Currently enrolling.

**Supplementary Information:**

The online version contains supplementary material available at 10.1186/s13063-024-08155-0.

## Background

To date, there have been more than 100 million SARS CoV-2 coronavirus infections in the USA, resulting in more than 1.1 million deaths and counting. Effective vaccines are now available [1], but the virus continues to mutate and circulate within the population, and there is an ongoing risk of future severe pandemic waves.

Symptomatic SARS CoV-2 infection can progress to a clinical syndrome termed coronavirus disease of 2019 (COVID-19). Severe COVID-19 is characterized by acute respiratory failure and development of the acute respiratory distress syndrome (ARDS). COVID-19 may be complicated by coagulopathy, acute cardiac injury, renal injury, and other systemic manifestations [2–5]. Approximately 20% of all hospitalized patients [6] and up to 40% of those admitted to the intensive care unit (ICU) die [7]. Moreover, around 15% of survivors [8] develop “long COVID” [9], a disabling condition which is more likely after severe acute illness [10].

Treatment options for severely ill patients with COVID-19 are limited. Remdesivir, immunomodulators such as tocilizumab and baricitinib, and corticosteroids have been shown to be of some benefit and are currently recommended for use, but supportive ICU care remains central to managing these patients. Specifically, administration of high concentrations of supplemental O_2_ and mechanical ventilation are often required [11, 12]. Supportive care is resource-intensive, and interventions such as O_2_ therapy and mechanical ventilation can themselves be injurious to the lung [13, 14]. Additional therapeutics to manage patients with COVID-19 and reduce the need for ICU care are therefore urgently needed.

Approximately 50% of the epithelial cells lining the alveoli in the distal lung are small cuboidal ATII cells [15]. ATII cells regulate the depth of the alveolar lining fluid by alveolar fluid clearance [16]. They also synthesize, secrete, and recycle pulmonary surfactant proteins and lipids (including phospholipids), which help to maintain low alveolar surface tension [17], reducing dynamic alveolar collapse and preventing gas exchange impairment during ventilation. Surfactant phospholipids also have anti-inflammatory properties, and surfactant proteins play an important role in host defense against pathogens [18]. ATII cells are thus essential to normal lung function and host defense and play a central role in ARDS pathogenesis.

ATII cell dysfunction and death in ARDS results in reduced surfactant production and function, leading to poor lung compliance, predisposition to ventilator-induced lung injury (VILI), impaired pathogen clearance, and enhanced inflammation [19–24]. ARDS also results in impaired alveolar fluid clearance [25], which is associated with a poor prognosis [11, 26]. Importantly, human ATII cells express the receptor for CoV-2 (ACE2) [27] and the protease cofactor TMPRSS2 [28] and SARS CoV-2 antigens have been detected in ATII cells from COVID-19 autopsy samples [29–33]. SARS CoV-2 has also been shown to replicate in ATII cells in vitro [34–36]. In addition to inducing release of inflammatory mediators [37], SARS CoV-2 infection of ATII cells may result in disruption of surfactant synthesis and alveolar fluid clearance, both of which may contribute significantly to development of COVID-19 [38, 39].

The phospholipid dipalmitoyl-phosphatidylcholine (16:0/16:0) is the largest component of pulmonary surfactant [40]. Dipalmitoyl-phosphatidylcholine is synthesized by the Kennedy pathway [41]. Synthesis of the liponucleotide cytidine 5’-diphospho (CDP)-choline from choline phosphate and CTP by the enzyme CTP-phosphocholine cytidylyltransferase-α (CCT-α) is rate limiting for this pathway. We showed that murine ATII cell CDP-choline synthesis is rapidly and completely inhibited by IAV infection in vivo [42]. Although we have not yet shown that SARS CoV-2 also inhibits ATII cell CDP-choline synthesis, multiple groups have reported that plasma or serum from COVID-19 patients contains reduced phosphatidylcholine [43–48], suggesting that SARS CoV-2 disrupts this pathway. Moreover, some of the beneficial effects of dexamethasone in COVID-19 patients could be because it stimulates CCT-α activity [49–56], as does CDP-choline [57].

We hypothesize that impaired ATII cell CDP-choline synthesis is a common feature of viral ARDS, which contributes significantly to its pathogenesis. Hence, we propose that the de novo phospholipid synthesis pathway is a promising target for host-directed therapy for viral ARDS. In support of this, we have shown that CDP-choline strongly attenuates IAV-induced ARDS and pulmonary inflammation [58] and prevents hypoxemia in SARS CoV-2-infected male K18-hACE2-Tg mice (unpublished data). Hence, we propose that this compound will be effective in COVID-19 patients. The pharmaceutical form of CDP-choline is citicoline.

SCARLET has two goals. Firstly, we will show that i.v. citicoline administration is safe over a range of doses in hospitalized SARS CoV-2-infected patients with hypoxemic acute respiratory failure (HARF). Secondly, we will obtain preliminary evidence that i.v. citicoline improves outcomes in this patient population relative to current standard of care and identify the recommended dose and appropriate clinical endpoints for larger Phase 3 efficacy trials. We will use a placebo control to represent current standard of care. We expect to find that citicoline is safe at all tested doses in COVID-19 patients. We also expect to find that citicoline has clinical benefit at one or more doses.

## Methods

### Participants, interventions, and outcomes

#### Study design and setting

SCARLET is a single-center, double‐blinded, placebo‐controlled, and randomized Phase 1/2 trial of i.v. citicoline in adult patients of any sex, gender, age, or ethnicity who are hospitalized with HARF following SARS CoV‐2 infection (Table 1). Patients will be enrolled at The Ohio State University (OSU) Wexner Medical Center (OSU WMC) and OSU WMC Hospital East (OSU East), both of which are in Columbus, Ohio, USA. The goals are to confirm citicoline safety over a range of doses and demonstrate potential for efficacy in this population for at least one citicoline dose. The trial will enroll 20 patients per dose for 3 citicoline doses (0.5, 2.5, and 5 mg/kg every 12 h for 5 days) along with 20 placebo‐treated controls (See Fig. 1).

**Table 1 Tab1:** WHO trial registration dataset

**Primary Registry and Trial Identifying Number**	Clinicaltrials.gov: NCT05881135
Date of Registration in Primary Registry	5/31/2023
Secondary Identifying Numbers	Federal Award Identification Number: U01AI677784 FDA IND: 162,806 OSU IRB protocol number: 2022H0451
Source of Monetary Support	NIAID Co-operative agreement
Primary Sponsor	[name] [name], MD
Secondary Sponsor(s)	None
Contact for Public Queries	[name] [name], MD Professor, Dept. of Internal Medicine, The Ohio State University [contact] [name]
Contact for Scientific Queries	Principal Investigators: [name] [name], MD Professor, Dept. of Internal Medicine, The Ohio State University [contact] [name] [name] [name], DVM, PhD, ATSF Professor, Dept. of Veterinary Biosciences, The Ohio State University [contact] [name] [name]
Public Title	Citicoline for hospitalized COVID patients
Scientific Title	SCARLET (Supplemental Citicoline Administration to Reduce Lung injury Efficacy Trial)
Countries of Recruitment	United States of America
Health Condition Studied	COVID-19
Intervention	Investigative agent: 0.5, 2.5, or 5 mg/kg) of Somazina® citicoline (CDP-choline) solution for injection (Ferrer Internacional, S.A., Barcelona, Spain) diluted in sterile USP-grade normal saline to 10 ml final volume, administered i.v. every 12 h for 5 days Placebo: 10 ml sterile USP-grade normal saline, administered i.v. every 12 h for 5 days
Key Inclusion and Exclusion Criteria	Inclusion Criteria: (1) Hypoxemic acute respiratory failure plus evidence of active SARS CoV-2 infection (positive for SARS CoV-2 using antigen or PCR test within the 10 days prior to randomization) (2) C-reactive protein > 32 mg/dl Exclusion Criteria: (1) Prisoners (2) Women who may be pregnant, are pregnant, or who are breast feeding (3) Subjects who are unable or unwilling to give written informed consent or to comply with study protocol and who have no legal authorized representative (LAR) available to give consent on their behalf (4) Individuals with a known allergy to citicoline (5) Subjects that are taking medications that contain L‐Dopa, centrophenoxine, or meclofenoxate (6) Individuals with hypertonia of the parasympathetic nervous system (7) Subjects who, in the clinicians estimation, will be unlikely to survive the protocol duration due to imminent and unavoidable risk of death (8) Individuals being treated with extracorporeal membrane oxygenation (ECMO) (9) Individuals with multiple organ failure
Study Type	Single-site, double-blinded, placebo-controlled, and randomized Phase 1/2 dose-ranging and safety study
Date of First Enrollment	7/14/2023
Sample Size	Planned: 80 Enrolled: 15
Recruitment Status	Recruiting
Primary Outcome	A statistically significant difference in lowest recorded S_p_O_2_:F_i_O_2_ ratio on study day 3, at *P* < 0.05
Key Secondary Outcomes	Statistically significant differences (*P* < 0.05) in: (1) Lowest recorded S_p_O_2_:F_i_O_2_ value on study days 1–2 and 4–8, or until extubation (whichever comes first) (2) Lowest Sequential Organ Failure Assessment (SOFA) score on study days 1, 3, 5, and 8 (3) Highest COVID Ordinal Outcomes Scale score on study days 1, 3, 8, 15, and 29 Oxygen-free days through day 28 Ventilator-free days through day 28 ICU-free days through day 28 Hospital-free days through day 28
Ethics Review	Approved by The Ohio State University Biomedical Sciences Institutional Review Board on 3/28/23 [name] [contact]
IPD sharing statement	Plan to share IDP: Yes All data will be deposited to the Dataverse that is supported by Harvard University under waivers providing for public availability of data repository starting 12 months after the trial begins and will be deposited every six months thereafter. This repository provides metadata, persistent unique identifiers, and long-term access for at least 10 years

**Fig. 1 Fig1:**
[figure not shown]
Trial design. SCARLET is a single-center, double‐blinded, placebo‐controlled, and randomized Phase 1/2 trial of i.v. citicoline in adult patients of any sex, gender, age, or ethnicity who are hospitalized with HARF following SARS CoV‐2 infection. The trial will enroll 20 patients per dose for 3 citicoline doses (1, 5, and 10 mg/kg/day, split into 2 doses 12 h apart) along with 20 placebo (sterile saline)‐treated controls

#### Eligibility criteria

Adult patients (≥ 18 years) of both sexes and any race or ethnicity will be eligible for enrollment. Research personnel (physicians and research coordinators) will screen patients daily for eligibility daily under partial HIPAA waiver using the electronic medical record (EMR; Epic, Madison, WI, USA) to facilitate identification of SARS CoV-2-positive patients who may meet other eligibility criteria for the trial. Enrollment is feasible any time during the hospital stay; however, if hospital discharge is anticipated within 24 h the patient will not be enrolled. Patients previously screened and not meeting inclusion criteria or with exclusion criteria may be rescreened daily until eligibility expires (> 10 days post admission).

Initial screening will assess for evidence of HARF plus evidence of active SARS CoV-2 infection. Only patients positive for SARS CoV-2 using antigen or PCR test within the 10 days prior to randomization will be eligible. Patients must also have a C-reactive protein > 32 mg/dl. Assurance of adequate peripheral or central venous access is a requirement. Female subjects of childbearing potential must have a negative pregnancy test upon study entry.

Patients meeting inclusion criteria will be screened for exclusion criteria. Individuals who meet any of these criteria are not eligible for enrollment as study participants: (1) Prisoners; (2) Women who may be pregnant, are pregnant, or who are breast feeding; (3) Subjects who are unable or unwilling to give written informed consent or to comply with study protocol and who have no legal authorized representative (LAR) available to give consent on their behalf; (4) Individuals with a known allergy to citicoline; (5) Subjects that are taking medications that contain L‐Dopa, centrophenoxine, or meclofenoxate; (6) Individuals with hypertonia of the parasympathetic nervous system; (7) Subjects who, in the clinicians estimation, will be unlikely to survive the protocol duration due to imminent and unavoidable risk of death; (8) Individuals being treated with extracorporeal membrane oxygenation (ECMO); (9) Individuals with multiple organ failure; and/or (10) Subjects with past or current medical problems or findings from physical examination or laboratory testing that are not listed above, which, in the opinion of the principal investigator (PI; [name]), may pose additional risks from participation in the study or that may impact the quality or interpretation of the data obtained from the study.

Critically ill children with SARS CoV-2 infection generally present with severe multisystem inflammatory syndrome (MIS-C) requiring vasoactive drugs and immunomodulators and are less likely to need ventilatory support than adults with severe COVID-19, who primarily develop progressive HARF which often leads to ARDS [59–62]. Hence, children will not be enrolled.

Following screening, eligible patients will be discussed with the patient’s primary care team. The ability to provide consent, directly or by a surrogate decision maker, will then be determined among patients who are deemed eligible. The patient or their LAR must be able to understand and provide informed consent. For subjects who are eligible for enrollment but are not recruited based on the clinician’s opinion that participation may not be in their best interests, the stated reason and name of the physician making the decision not to enroll will be recorded.

After approval from their care team, one of the study physicians or their official designee (a research coordinator) will approach the patient or their LAR if the patient is deemed unable to provide consent. The research study will be explained in lay terms in accordance with OSU standard operating procedures. Disclosures of potential conflicts of financial interest for the Institution and for [name] (who will not be involved in patient interactions or treatment decisions) will be included in the final consent form. Once informed consent has been obtained, subjects will be enrolled into the study and randomized using random block permutations. Randomization will be done by OSU WMC Investigational Drug Services (IDS) and all clinical and research personnel will be blinded to allocation. Randomization must occur within 24 h from time of consent.

A participant will be deemed to have completed the study following administration of their final dose of test agent (10 doses over 5 days), unless discharged earlier. Study participation may be prematurely terminated for the following reasons: (1) The participant elects to withdraw consent from all future study activities, including follow‐up; (2) The participant dies; (3) The PI no longer believes participation is in the best interest of the participant; or (4) The PI believes that a serious adverse event (SAE) in the patient may be attributable to the investigational agent.

Participants who withdraw or are withdrawn will not be replaced if they have received at least one dose of the investigational agent. No follow-up will occur for participants who withdraw or are withdrawn from the trial.

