#### Criteria for discontinuing or modifying allocated interventions

No modifications to the test agent dose or frequency will be permitted during the study period. Study therapy may be prematurely discontinued for any participant for any of the following reasons: (1) SAEs occur that, in the view of the attending clinician, study investigator, or PI, may be attributable to citicoline; (2) The PI believes that the study treatment is no longer in the best interest of the participant; or (3) The Data Safety Monitoring Board (DSMB) will make a determination of futility or potential for harm to the patient(s).

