**Fig. 2 Fig2:**
[figure not shown]
Individual patient schedule. Patients will receive test agent (citicoline or saline placebo) every 12 h for 5 days. Patients will be monitored out to day 29. ABGs—arterial blood gases; CBC/CHEM—complete blood count and chemistry panel; COOS—COVID Ordinal Outcomes Scale; CXR—chest X-ray; S:F—S_a_O_2_:F_i_O_2_ ratio; SOFA—Sequential Organ Failure Assessment

Day 0–1:Informed consent will be obtained.Order for study drug will be placed by the investigator.Initial clinical data will be obtained by research staff using the EMR and recorded in the REDCap study database. Missing laboratory data will be ordered by the investigator.Blood will be drawn from all patients prior to the first treatment dose for laboratory studies.Study drug will be administered i.v. by the bedside nurse operating within their usual scope of practice. The timing of study drug administration may be adjusted up to 4 h on subsequent dosing to achieve standard dosing times.Clinical information, including other drugs administered, will be recorded by the research team into the REDCap study database.

Days 1–5:The patient will be assessed daily by study team for evidence of adverse drug reactions.Dosing with the test agent will continue every 12 h until each subject has received 10 doses total.Laboratory samples will be collected according to the study timeline.Clinical information, including other drugs administered, will be recorded by the research team into the REDCap study database.

Days 6–8:The patient will be assessed daily by study team for evidence of adverse drug reactions or clinical change.Laboratory samples will be collected according to the study timeline.Clinical information, including other drugs administered, will be recorded by the research team into the REDCap study database.

Days 9–29:Patient will be assessed daily by study team for evidence of adverse drug reactions or clinical change.Patients discharged home prior to day 29 will be called on day 29 to verify vital status and discharge location.Patients who withdrew from the trial at any point prior to the cessation of test agent administration

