#### Participant stopping rules and withdrawal criteria

Participants may be prematurely terminated from the study for the following reasons: (1) The participant elects to withdraw consent from all future study activities, including follow‐up; (2) The participant dies; (3) The Investigator no longer believes participation is in the best interest of the participant; or (4) The Investigator believes that an SAE in the patient may be attributable to the test agent.

Participants who withdraw or are withdrawn will not be replaced if they have received at least one dose of the investigational agent.

Patients wishing to withdrawal early from the study (i.e., before all 10 doses were administered) will be asked if they are agreeable to follow-up phone call on day #29. If approval is granted, they will be called on day 29 to verify vital status and discharge location. Patients opting complete withdrawal from the study will not be contacted further.

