#### Recording of AEs

AEs will be collected from the time of first dose of study drug, until a subject completes study participation (day 29) or until 30 days after they prematurely withdraw (without withdrawing consent) or is withdrawn from the study. AEs (including SAEs) may be discovered through any of these methods: (1) Observing the subject; (2) Interviewing the subject; or (3) Receiving an unsolicited complaint from the subject. In addition, an abnormal value or result from a clinical or laboratory evaluation can also indicate an AE.

Throughout the study, the PI and his team will record Grade 2 or higher AEs on the appropriate AE/SAE or electronic case report form (eCRF) regardless of the relationship to study therapy regimen or study procedure. Once recorded, an AE will be followed until it resolves with or without sequelae, or until the end of study participation, or until 30 days after the subject prematurely withdraws (without withdrawing consent)/or is withdrawn from the study, whichever occurs first.

The relationship, or attribution, of an AE to the study therapy regimen or study procedure(s) will initially be determined by the PI and recorded on the appropriate AE (AE/SAE or eCRF). Final determination of attribution for safety reporting will be determined by the Medical Monitor, DSMB, PI, and NIAID*.*

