### Statistical analysis

All analysis will be based on intention to treat guidelines and reporting will follow CONSORT guidelines [65]. Data will be analyzed using STAT software (SAS; Cary, NC). The primary clinical outcome (S:F ratio on day 3) will be analyzed using either analysis of variance or a non-parametric Kruskal–Wallis test if analysis of variance assumptions (normality, homoscedasticity) are violated. Follow-up contrasts comparing each dose to control will be performed at *α* = 0.05/3 if the global test of differences between groups is rejected. If subject dropout due to mortality or discharge is present prior to day 3, the survivor average causal effect will employ a potential outcomes approach to account for potential survival bias and estimate the average causal effect of the intervention on S:F ratio among participants who would survive regardless of their intervention status, e.g., the always-survivors [66, 67]. The recommended citicoline dose for Phase 3 trials will be the dose achieving the greatest statistically significant improvement in day 3 S:F ratios, with consideration of key secondary endpoints (SOFA scores, etc.). Standardized mean differences will assess balance on baseline covariates across treatment arms. Competing risks analysis will assess differences between groups for competing time-to-event outcomes (e.g., hospital mortality, time to recovery, time off ventilator, discharge) [68].

Differences in SOFA scores between groups will be evaluated using non-parametric tests. A multinomial ordinal proportional odds model will estimate the odds ratio between study groups for COVID Ordinal Outcomes Scale. For outcomes with repeated assessments, generalized mixed models will evaluate differences between groups with a subject-level random effect to account for repeated measures. The mixed model accounts for data that are missing at random, when including baseline covariates associated with missing status. To account for potential non-ignorable dropout (e.g., due to mortality), a joint modeling approach will incorporate a shared random effect to simultaneously model the time-to-event process and longitudinal process [69].

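### The rule that nobody who leaves the trial is followed contradicts the adverse-event rule and, if applied to PI withdrawals, leaves randomised patients without later outcomes

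*Protocol article*

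**What the plan says.** All references are to the Protocol article.

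- **Eligibility criteria** lists four reasons for ending study participation. Two are withdrawal of consent to all future activities, follow-up included, and death. The other two are decisions by the PI: "The PI no longer believes participation is in the best interest of the participant" and "The PI believes that a serious adverse event (SAE) in the patient may be attributable to the investigational agent". It then adds, without exception: "No follow-up will occur for participants who withdraw or are withdrawn from the trial". Patients who have had at least one dose are not replaced.
- **Participant stopping rules and withdrawal criteria** repeats the four reasons. It then says that patients who wish to leave before all 10 doses "will be asked if they are agreeable to follow-up phone call on day #29", and it ends contact only for those who choose complete withdrawal.
- **Recording of AEs** collects adverse events to day 29 or "until 30 days after they prematurely withdraw (without withdrawing consent) or is withdrawn from the study".
- **Criteria for discontinuing or modifying allocated interventions** opens with "Study therapy may be prematurely discontinued for any participant for any of the following reasons". Its list includes a possibly attributable SAE and the PI's view of the patient's best interest.
- **Statistical analysis** states: "All analysis will be based on intention to treat guidelines".

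**The concern.** The site cannot follow all of these instructions. For a patient withdrawn by the PI, one section ends follow-up and another requires 30 more days of adverse-event collection. The section on discontinuing therapy adds a third possibility: the same SAE or the same best-interest judgement may stop study drug only and leave the patient in the trial. Nothing in the text decides which route applies.

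The choice matters because safety is one of the primary outcomes and the Phase 3 dose is to be chosen from comparisons between arms. Patients taken out for suspected toxicity, or because taking part no longer seems in their interest, are unlikely to resemble those who stay, and their number may differ by dose. If their data collection stops, intention to treat can be applied to them only with missing outcomes that the protocol itself chose not to collect.

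**Working it through.** **1. The rules side by side**

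| Situation | Eligibility criteria | Participant stopping rules | Recording of AEs |
|---|---|---|---|
| Consent withdrawn for everything, follow-up included | No follow-up | No contact | Outside the 30-day rule |
| Patient leaves early but accepts some contact | No follow-up | Day-29 call if agreed | AEs for 30 days |
| PI withdraws: best interest | No follow-up | Call not addressed | AEs for 30 days |
| PI withdraws: possibly attributable SAE | No follow-up | Call not addressed | AEs for 30 days |

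The first row is consistent. The second conflicts with two sections. The third and fourth conflict with Recording of AEs; the day-29 call is written for patients who wish to leave, so it does not settle their case.

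**2. What is lost if the no-follow-up sentence is obeyed**

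- Withdrawal before day 3: the primary efficacy outcome (day-3 S:F) and everything after it.
- Withdrawal on or after day 3: the remaining S:F values to day 8, the remaining SOFA assessments, the ordinal scale to day 29 and the four day-28 free-day outcomes.
- In either case: further adverse events and the later course of the SAE that led to withdrawal.

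**3. Does the analysis section cover it?** The survivor average causal effect for day-3 S:F is named for dropout through mortality or discharge. PI withdrawal is neither. The mixed model for repeated outcomes assumes data missing at random. The joint model for non-ignorable dropout gives mortality as its example and serves longitudinal outcomes, not the day-3 analysis of variance or Kruskal–Wallis test.

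**4. Scale**

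The plan's own figure comes first. The sample-size text (under Protocol modifications) gives 80 participants, 5% missing at day 3, overall effect size f = 0.39, α = 0.05 and 80% power. For a four-group analysis of variance, power = P(F′ > F_crit) with 3 and N − 4 degrees of freedom and noncentrality λ = N·f².

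- Evaluable N = 80 × 0.95 = 76, so λ = 76 × 0.1521 = 11.56 and power is 80.2%. The stated figure reproduces.
- The allowance is 80 × 0.05 = 4 patients, or one per arm of 20 (1/20 = 5%).

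The documents give no withdrawal rate, so the other rows below are illustrations.

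| Day-3 values lost | N observed | λ | Power |
|---|---|---|---|
| 0% | 80 | 12.17 | 82.5% |
| 5% | 76 | 11.56 | 80.2% |
| 10% | 72 | 10.95 | 77.6% |
| 15% | 68 | 10.34 | 74.8% |

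The power loss is modest. Bias works differently. If one unobserved patient would have had an S:F value Δ below the observed mean m of the other 19, the full-arm mean is (19m + m − Δ)/20 = m − Δ/20, so the observed mean is too high by Δ/20. Neither Δ nor the number of such patients is known.

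**5. Effect on the Table 2 safety rule.** The rule uses Pr(p > 0.25 | data) > 0.85 with a Beta(1, 1) prior, and the count is of patients with an SAE. Seven of 20 gives Beta(8, 14) and a posterior probability of 0.870; six of 20 gives Beta(7, 15) and 0.744. The limit of 7 therefore reproduces. A patient withdrawn because of an attributable SAE is already in that count, and a second SAE in the same patient would not change it.

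**The case against.** The best defence is that the effect is limited, and several stronger readings do fail.

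- **A toxic dose could pass as safe because its patients vanish.** A reader might infer this, but the documents do not support it for SAE-triggered withdrawals, which Table 2 has already counted. Only an SAE arising after a best-interest withdrawal could be missed, and only if Recording of AEs is disregarded.
- **Up to 30% of an arm could go unfollowed.** Six of 20 is the largest count that Table 2 lets pass. It is not a forecast, and the protocol regards serious reactions as unlikely.
- **The plan contradicts intention to treat.** That is a principle of analysis. Leaving outcomes uncollected undermines it in practice, but no two statements conflict literally.
- **Clinical deterioration removes patients from the trial.** It is not a listed reason for leaving. Interim safety analysis treats it as a possible reason for stopping study drug, and respiratory worsening consistent with COVID-19 is still entered in the study database. It could end participation only through the discretionary best-interest reason.
- **The plan has no answer to informative dropout.** It has the joint model, and mortality is given there only as an example.

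It is also true that ending participation is permitted rather than automatic, that a therapy-only route already exists, and that ending follow-up is proper when consent to it is withdrawn. For discharged patients, the Participant timeline says they "will be called on day 29 to verify vital status and discharge location". Whether that call should ask more is a separate matter of detail that a journal article may leave to the full protocol.

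What stands is the conflict itself. This is not detail lost in condensing: the article states a rule without exception and elsewhere states its opposite.

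**Conclusion.** The point holds as an inconsistency with a consequence for the data. The no-follow-up sentence contradicts Recording of AEs for anyone the PI withdraws, and contradicts both that section and the day-29 call for patients who leave early without refusing all contact. The overlap with the therapy-only triggers lets the same event produce either full follow-up or none.

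If the sentence governs, the later outcomes and adverse events of these patients are not collected, nor is day-3 S:F when withdrawal comes first. That this loss depends on treatment and outcome is a judgement from the listed reasons; the documents offer no data on it. Its size is unquantified: one patient is 5% of an arm and equals that arm's share of the day-3 missing-data allowance. The likely harm is bias in later outcomes and in some day-3 values, more than lost power. The count of patients with SAEs in Table 2 keeps every triggering SAE. No change in sample size follows.

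**What to change.** Delete the no-follow-up sentence from Eligibility criteria. Reconcile that section with Criteria for discontinuing or modifying allocated interventions, Participant stopping rules and withdrawal criteria, and Recording of AEs, so that stopping study drug and ending data collection are separate events. When study drug should stop is a clinical matter on which this point takes no position.

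State that data collection ends early only on death or withdrawal of consent to follow-up. For every other patient, collect day-3 S:F, the secondary outcomes and adverse events through at least day 29, and for the full 30 days after withdrawal where Recording of AEs requires it. The sources are the medical record, from which study data are already taken, and the existing day-29 call.

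The cost is a protocol amendment and slightly more data abstraction. Under Protocol modifications, the amendment needs consultation with the DSMB and approval by the IRB and FDA. Table 1 shows 15 of 80 patients enrolled, so at that point the change would have covered the remaining 65.
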